**Research Protocol**

Synopsis

This pragmatic trial with cluster randomization of AEDs is designed to evaluate the effectiveness and cost-effectiveness of screening methods (modified PAT vs FAST vs modified SASQ) and interventions (Leaflet vs Brief advice vs Brief counselling) in routine AED care. Due to the design implications of a multi-level factorial design in AEDs the proposed trial involves a universal screening approach in which relevant data for a sub-sample of linked presentation population is collected. Therefore, the trial design encompasses a 3x3 factorial trial, screening method (modified PAT vs FAST vs modified SASQ) and intervention (Leaflet vs Brief advice vs Brief lifestyle counselling). The main advantages of utilising a factorial approach are twofold. First each of the three elements (screening tool and intervention) can be analysed independently with sufficient power to make meaningful interpretation of relative effectiveness. Second, the method enables meaningful interpretations of the relative effectiveness of any combination of screening method and intervention. Because the universal screening population encompasses a sub-group of linked presentation targeted population we can make meaningful comparisons of the relative effectiveness and interactions associated with screening approach in AEDs. Nine AEDs across the North East, London and the South East Regions of England will be recruited. AEDs will be randomly allocated to one of three intervention conditions: the patient information leaflet control condition (n=3), the structured brief advice condition (n=3); and lifestyle counselling by an Alcohol Health Worker (n=3). To test the relative effectiveness of different screening methods all AEDs will be randomised to either a modified single item screen (Single Alcohol Screening Question; M-SASQ) or a modified Paddington Alcohol Test (SIPS-PAT) or FAST Alcohol Screening Test (FAST) screening method. AEDs in the modified PAT condition will use targeted screening as per the standard PAT protocol. AEDs in the FAST and modified SASQ conditions will use universal screening for case identification and collect information about whether a patient would be part of a linked presentation group and then use statistical simulation to analyse any interactions. Screening randomisation will be stratified by median AED admission rates (2 levels) and intervention condition (3 levels). Each AED will recruit a minimum of 131 patients who are hazardous or harmful drinkers into the trial and a short baseline assessment will be carried out. Outcome will be assessed at 6, and 12 months after intervention. Outcomes will include system implementation outcomes and patient outcomes. We will also examine the practitioner and organisational factors associated with successful implementation.

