
Study aim

To evaluate the implementation, effectiveness and cost effectiveness of BI delivered by an alcohol health worker aimed at reducing excessive drinking in routine AED care compared to brief advice and a patient information leaflet (PIL) in hazardous and harmful drinkers identified by universal or targeted screening.

Study objectives

- To conduct a pragmatic multicentre cluster randomised controlled trial of screening and brief interventions for hazardous and harmful drinkers in AEDs in three English regions.
- To compare the effectiveness and cost effectiveness of brief advice conducted by AED staff (including dedicated AHWs) (Tier 1) with referral to an alcohol health worker (Tier 2) of patients with hazardous and harmful alcohol consumption identified by targeted opportunistic or universal screening.
- To assess the relative impact of the three implementation strategies on alcohol screening and brief intervention activity in AEDs.
- To identify the attitudinal, practical, skill, resource, and reinforcing factors that predict successful implementation of screening and brief intervention in AEDs.
- To identify the optimal method of alcohol screening in AED.
- To assess the relative impact of the three implementation strategies on uptake of alcohol services, including an alcohol helpline.

Hypotheses

- Brief Lifestyle Counselling intervention by an alcohol health worker for hazardous and harmful drinkers identified by targeted screening is more effective and cost effective than Brief Advice conducted by AED staff (including dedicated AHWs) in the typical AED setting.
- Brief Lifestyle Counselling intervention by and alcohol health worker and Brief Advice by AED staff (including dedicated AHWs) are more effective and cost effective than an information leaflet alone.
- Access to referral to an alcohol health worker results in greater screening and intervention activity than training of AED staff in screening and brief intervention alone.
- Attitudinal, practical, skill, resource, and reinforcing factors predict screening and intervention activity.
- Briefer screening methods result in greater implementation of screening activity than more complex methods.

Setting

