The AED study design differs from the PHC study in not having targeted versus universal screening as a separate factor in the design. There are two main reasons for this. First, we have looked closely at the potential of a factorial design including universal versus targeted screening. However, the number of AEDs that would be required to have a separate screening factors (minimum n=18) would exceed the likely number of AEDs agreeing to participate in the there regions (based on previous experience from our national AED survey (Drummond et al., 2003)). Second the PAT has been designed as a targeted screening method in the context of routine AED assessment. The FAST and SASQ on the other hand have been designed as universal screening tools. Therefore we propose that universal versus targeted screening be studied in two ways within this trial. First we will randomize AEDs to targeted screening with the modified PAT and universal screening with FAST or the modified SASQ, which is appropriate to the design of the instruments. Second we will record the patients’ presenting clinical conditions and demographic factors in the universal screening arms of the study to identify which factors are most strongly associated with alcohol positive cases. Together these findings will allow the comparison of targeted and universal screening and lead to the development of clinical guidelines for AEDs on the most efficient form of targeted screening approach.

Table **1**. Overall AED study design.

| Intervention condition **>** | Leaflet by AED staff | Brief advice by AED staff | Brief Lifestyle  Counselling intervention | Totals |
| --- | --- | --- | --- | --- |
| Screening condition V |
| FAST Alcohol Screening Test | AED n=1;  Patients n=131 | AED n=1;  Patients n=131 | AED n=1;  Patients n=131 | AED n=3;  Patients n=393 |
| Modified Single Alcohol Screening Question | AED n=1;  Patients n=131 | AED n=1;  Patients n=131 | AED n=1;  Patients n=131 | AED n=3;  Patients n=393 |
| SIPS Paddington Alcohol Test | AED n=1;  Patients n=131 | AED n=1;  Patients n=131 | AED n=1;  Patients n=131 | AED n=3;  Patients n=393 |
| Total per intervention | AED n=3  Patients n=393 | AED n=3  Patients n=393 | AED n=3  Patients n=393 | AED n=9  Patients n=1179 |

Screening conditions

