However, it is unclear which approach is most effective in identifying cases in the typical AED setting. The modified PAT (SIPS-PAT) is a targeted screening tool which is applied in cases with presenting conditions commonly associated with alcohol misuse. The original PAT has been used at St Mary’s Hospital embedded in the standard clinical assessment process. SASQ on the other hand has been studied in PHC and, based on our pilot research, is more likely to be adopted by busy AED staff. The FAST has been used mainly in a research screening context to establish prevalence rather than as a clinical tool. Also this single question in the modified SASQ will identify individuals whose level of drinking is more likely to lead to AED attendance, and is the same first item of the FAST questionnaire, which was found to identify 50% of hazardous and harmful drinkers (Hodgson et al., 2002).

Brief intervention implementation conditions

1. *Control condition:* AED staff (including dedicated AHWs) in the control condition will be trained to apply the appropriate screening method and record the screening outcome, will feedback the result of screening to patients and offer them a patient information leaflet (PIL. The PIL from the Drink-Less Programme and has been extensively pre-tested with clinicians and patients in PHC and will be used in this trial. The PIL will also contain a number for Drinkline where the patient can access further information). The PIL to be used in this trial will be ‘Alcohol and Sensible Drinking’ as in the PHC study.

2. *Brief Advice condition:* AED staff (including dedicated AHWs)will be trained to carry out screening and deliver up to 5 minutes of simple structured brief advice for hazardous and harmful drinkers presenting to the AED, using the Drink-Less brief intervention materials (level 1) as in the PHC study. Patients in this condition will also receive a Patient Information Leaflet (PIL) as above, including a number for Drinkline.

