The research team will identify the total number of patients over 18 attending each AED during the recruitment period, the total number of patients screened, the number screening positive, and the number receiving an alcohol intervention (either a leaflet or brief advice by AED staff (including dedicated AHWs)or brief lifestyle counselling intervention by the AHW) according to the method described by Babor et al. (2005). This will allow calculation of the overall screening rate, the screen conversion rate (proportion of positive screens), and the intervention rate in the different settings. We will also compare these measures between AEDs assigned to the SIPS-PAT versus the modified SASQ versus FAST screening methods.

Reattendence to AEDs over the 6, and 12 month follow up period of patients participating in the study will be assessed using computerised admission records and compared with admissions by the participating group of patients in the 6 month before entry into the study. The sustainability of the screening and intervention approaches will be assessed by examining the extent to which screening and intervention activity continues after the end of the formal study recruitment period.

Patient measures:

*Baseline*

Before receiving the initial PIL and/or brief advice intervention and/or brief lifestyle counselling intervention, participants will be invited by AED staff (including dedicated AHWs) to provide the contact details and complete the Extended AUDIT, EQ5D, Short-SUQ and modified Readiness to change Ruler. Participants in the extended intervention will complete the AUDIT at the same stage as those in other groups.

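### The screening and conversion rates compared between SIPS-PAT, M-SASQ and FAST departments mix the tool with targeted versus universal screening, and the listed counts do not separate the two

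*Protocol*

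**What the plan says.** Under System measures the protocol lists four counts per department: "the total number of patients over 18 attending each AED during the recruitment period, the total number of patients screened", then the number screening positive and the number given an intervention. It continues: "This will allow calculation of the overall screening rate, the screen conversion rate (proportion of positive screens), and the intervention rate in the different settings". The conversion rate therefore has patients screened as its base. The base of the screening rate is not written out, but adult attenders is the only listed count that fits. The base of the intervention rate is not stated. The section then says: "We will also compare these measures between AEDs assigned to the SIPS-PAT versus the modified SASQ versus FAST screening methods".

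Who is screened depends on the tool. The Synopsis says: "AEDs in the modified PAT condition will use targeted screening as per the standard PAT protocol". The Screening conditions section says the SIPS-PAT "is a targeted screening tool which is applied in cases with presenting conditions commonly associated with alcohol misuse". The Design section ties tool to approach on purpose: "First we will randomize AEDs to targeted screening with the modified PAT and universal screening with FAST or the modified SASQ".

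These measures serve the objective of finding the optimal screening method and the hypothesis: "Briefer screening methods result in greater implementation of screening activity than more complex methods".

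**The concern.** Staff in a SIPS-PAT department are told not to screen patients whose presentation falls outside the target group. If those patients stay in the denominator, the department's screening rate is held down by instruction, not by anything about the tool or the staff's willingness to use it. The conversion rate has a different problem. SIPS-PAT is applied to presentations chosen for their link with alcohol, so its proportion positive comes from a selected case-mix.

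At stake is how the tool comparison is read. The hypothesis attributes screening activity to brevity. The Screening conditions section says the PAT was itself cut to two questions, so a low SIPS-PAT screening rate could count against the brevity hypothesis merely because most attenders were out of scope. A high SIPS-PAT conversion rate could be taken as better case-finding when it reflects who was asked. The primary outcome is not affected.

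**Working it through.** The protocol gives no figure for any of these rates, so there is nothing to reproduce. The check is algebraic. Every input below is an assumption, because the protocol supplies none of them.

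Inputs:
- s, the share of adult attenders with a linked presentation: 0.2 to 0.6.
- u, the uptake among patients whom staff are told to screen: 0.3 to 0.8, taken in universal departments to be the same for linked and other presentations.
- pT and pN, the proportions positive in linked and other presentations: from 0.4 and 0.4 (no enrichment) to 0.6 and 0.2. The tools are taken to perform identically.

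**Screening rate on all adult attenders.** SIPS-PAT: s × u. Universal: u. At equal uptake the ratio is s.

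| s | u | SIPS-PAT | Universal | Ratio |
|---|---|---|---|---|
| 0.2 | 0.5 | 10% | 50% | 0.2 |
| 0.4 | 0.5 | 20% | 50% | 0.4 |
| 0.6 | 0.5 | 30% | 50% | 0.6 |

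With linked attenders as the base in every department, the ratio at equal uptake is u / u = 1.0.

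**Cap or fixed result?** To match a universal uptake u, SIPS-PAT staff need an uptake of u / s among linked patients.
- s = 0.2, u = 0.3: 0.3 / 0.2 = 1.5, which is impossible.
- s = 0.4, u = 0.5: 0.5 / 0.4 = 1.25, which is impossible.
- s = 0.4, u = 0.3: 0.3 / 0.4 = 0.75, which is possible.
- s = 0.6, u = 0.3: 0.3 / 0.6 = 0.50, which is possible.

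The rate is capped at s, but the ranking is not settled in advance.

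**Conversion rate among patients screened.** SIPS-PAT: pT. Universal: s × pT + (1 − s) × pN.

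| s | pT | pN | SIPS-PAT | Universal | Ratio |
|---|---|---|---|---|---|
| 0.4 | 0.4 | 0.4 | 40% | 40% | 1.00 |
| 0.4 | 0.5 | 0.25 | 50% | 0.20 + 0.15 = 35% | 1.43 |
| 0.6 | 0.6 | 0.2 | 60% | 0.36 + 0.08 = 44% | 1.36 |
| 0.2 | 0.6 | 0.2 | 60% | 0.12 + 0.16 = 28% | 2.14 |

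Restricted to linked presentations, both arms give pT and the ratio is 1.0.

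**Intervention rate.** If its base is positive screens, the cap does not apply. If its base is attenders, it does. The protocol does not say which.

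**The case against.** The protocol does not hide the tie between tool and approach. The Design section explains that a separate targeted-versus-universal factor would need at least 18 departments, and that each tool is used as it was designed to be used. The Synopsis plans a linked-presentation flag in the FAST and M-SASQ departments, the Design section plans to record presenting conditions there, and the Planned analysis section adds simulations covering both approaches. The three-way comparison already contains M-SASQ versus FAST, where both arms are universal and no cap arises. In a pragmatic trial, lower coverage is a real property of targeted screening, so an all-attender rate is a fair result for tool and approach together. Exact denominators are often left to an analysis plan, which is not shown here.

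Most of this stands, and it limits the point. It does not remove it. System measures neither applies the flag to these rates nor labels the SIPS-PAT contrasts as tool plus approach. The flag could support a restricted conversion comparison. It does not clearly supply the number of linked attenders, screened or not, in SIPS-PAT departments, because the recording is described for the universal arms only. An analysis plan cannot create a denominator that was never counted.

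A reader might also infer that all three measures use adult attenders as their base, or that SIPS-PAT must look poorly used and more accurate whatever its merits. The protocol does not support this. Conversion is defined on screens, the intervention-rate base is unstated, and the screening rate still depends on uptake. At s = 0.6, full SIPS-PAT uptake gives 60% against 50% for a universal department with half uptake. Nor does the protocol treat conversion as accuracy; it discusses accuracy separately, as sensitivity and specificity.

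**Conclusion.** The point holds in limited form. As written, the screening and conversion rates compared between SIPS-PAT and the two universal tools do not isolate the tool. On the only attendance count listed, the SIPS-PAT screening rate is capped at s, and at equal uptake it is s times the universal rate: a ratio of 0.2 to 0.6 for assumed s of 0.2 to 0.6. The conversion rate leans the other way if linked presentations are more often positive, with a ratio of 1.0 to 2.14 over the assumed inputs. The existence of the cap follows from the protocol's text, given that adult attenders is the base; its size cannot be stated without s. The M-SASQ versus FAST comparison is unaffected. These are secondary system measures, but they bear on a named objective and hypothesis, so the change should be made.

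**What to change.** Amend System measures as follows.

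1. Compare conversion between tools within linked presentations, using the flag already planned in the universal departments. This needs no new data there.
2. Test the brevity hypothesis mainly as M-SASQ versus FAST. Both are universal, and the protocol describes the M-SASQ question as the first FAST item.
3. Report all-attender rates involving SIPS-PAT as results for tool plus approach, not as tool effects.
4. Where departmental records allow, count linked-presentation adult attendances at all nine departments, screened or not, and compare screening rates on that base.
5. State the base of each rate, including the intervention rate.

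Items 1, 2, 3 and 5 are changes of wording and analysis. Item 4 needs extra record extraction, and the protocol does not show that it is possible at every site. If it is not, the conclusion about SIPS-PAT uptake has to be narrower.

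A related inconsistency should be reconciled at the same time. The Brief Lifestyle condition is described as training staff in universal screening, yet Table 1 places one SIPS-PAT department in that condition and the Synopsis describes SIPS-PAT screening as targeted.

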Nine AEDs in three English regions (North East, London, South East) will be recruited to take part in the study. Recruitment will take place with the assistance of the British Association of Accident and Emergency Medicine (BAEM, of which [name] is a Professor of Accident and Emergency Medicine and adviser to BAEM on the management of alcohol misuse). All AEDs in the three regions that do not have current routine alcohol screening and brief intervention facilities will be eligible to participate. AEDs will be selected to provide a range of both urban and rural catchment areas.

Design

AEDs will be randomly allocated to one of three implementation conditions (leaflet, brief advice or brief lifestyle counseling intervention) in a cluster randomized design such that there will be 3 AEDs in each condition. AEDs will be randomized to one of three screening conditions (described below) such that there will be 3 AEDs in each condition (see Table **1**). Patients enrolled in the study will have a baseline research assessment carried out by structured interview, and followed in parallel groups over 6, and 12 months. Outcome assessment will be by face to face or telephone interview conducted by a researcher.

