In the Brief Lifestyle Counselling condition the training and support for AED staff will be the same as in the simple structured advice condition except that staff will be trained to screen and refer to the AHW. The equivalent of approximately 0.5 WTE AHW salary per AED has been allocated. In some areas it may be more practical to have one AHW split between two AEDs. In other areas different configurations can apply. The AHW will be responsible for training and supporting the AED staff in implementing screening and referral over the course of the project. The AED staff will also be supported in implementation of the screening and research procedures by a member of the research team.

Inclusion criteria

AEDs: Eligible AEDs will be those not already providing routine screening and SBI.

Patients: Any AED patients scoring positive on the modified PAT, FAST or modified SASQ aged 18 or over, and who are alert and orientated, resident within 20 miles and able to speak, read and write English sufficiently well to complete study questionnaires.

Exclusion criteria

Those who are currently seeking help for alcohol problems and those who are involved in any alcohol research study will be excluded. Any patients within the AED setting who are severely injured, suffering with a serious mental health problem and/or who are grossly intoxicated will also be excluded from the study. Finally patients with no fixed abode will be excluded from the study.

Consent

Consent to participate will be obtained in a 2 stage process. AED staff (including dedicated AHWs) will initially establish verbal consent to be check eligibility to take part, collect some basic demographic information and to be screened. Those who then are positive on FAST or modified SASQ or SIPS-PAT as applicable, will have the study explained to them verbally by AED staff (including dedicated AHWs) and in writing (using the patient information sheet). Written informed consent will be obtained by AED staff (including dedicated AHWs). This will include permission to give the patient's data and contact details to the research staff, and provide the research team with access to the patients AED records, and to participate in follow up after 6, and 12 months. The research team will then contact the patient within two weeks to thank him/her to take part in the study.

Measures

Staff attitudinal and organisational measures:

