Patients’ use of health, social care and criminal justice services will be identified retrospectively using a short form of the Service Use Questionnaire and applying a common set of national unit cost estimates. Patient costs in the 6 month period before SBI can then be compared to cost in the 6 month period after SBI to explore any changes in costs imposed by patients in each group.

The economic analysis will calculate the incremental cost-effectiveness of the control condition with the AHW condition under study, using measures of clinical outcome and quality of life (EQ-5D; The EuroQoL Group, 1990) responses at baseline and at 6 and 12 month follow ups. The use of EQ-5D enables the estimation of Quality Adjusted Life Years. Data will be bootstrapped to account for the expected skewness evident in economic cost data (National Institute for Clinical Excellence, 2004). The analysis will include the construction of cost-effectiveness acceptability curves to illustrate the probability that the brief intervention is more cost-effective than usual care, based on different monetary values being attached to QALYs. The use of QALYs follows the recommendations of NICE(Briggs & Gray, 1999) and enables the value for money afforded by treatment to be compared to a range of other health care interventions. Furthermore, combination of the economic cost data and outcome data with patient data collected in the trial will enable a secondary analysis of various patient characteristics that may influence the cost-effectiveness of the intervention.

Incentives

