The sample size calculation is designed to account primarily for intervention level outcomes. Powering the study in this way will also account statistically for appropriate outcomes for screening approach and screening method. The primary outcome for this study is the proportion of patients who consume alcohol within recommended levels at 6 month follow up. Recent meta-analysis (Moyer et al 2002) suggest that the difference between brief intervention and control is of the order 13%, 5% reduction in the control group and 18% in the brief intervention group. In order to detect a difference of this magnitude at the 5% significance level with 80% power, for a 2-sided test, requires 109 patients in each of the 3 groups, a total of 327. Our experience with other multi-centre randomized controlled trials of interventions for alcohol use disorders suggests that with assiduous follow-up the potential loss to follow-up across groups is of the order 25%. Taking this loss into accounts inflates the sample required to 131 in each group, a total of 393 patients per intervention.

The proposed study involves a cluster design and requires a statistical adjustment to account for any potential cluster effect. The literature, and our previous experience of trials in primary care, suggest an intra-class correlation coefficient of 0.04 is appropriate. Assuming a cluster size of the order 131 patients this inflates the sample size calculation by a factor of 2.7 requiring patients 393 in each group, a total of 1179, with an expectation that at least 882 will be followed up at 6 months.

We propose to recruit 9 AED’s. AED populations will be screened using 1 of 3 screening method groups (3 AED’s in each group) and will receive 1 of 3 intervention (3 AED’s in each group).

Planned analysis

As the study is pragmatic in design, the planned analysis will be by intention to treat. The primary outcome is dichotomous in nature, drinking within or above recommended levels, and will be analysed logistic regression adjusting for all known prognostic factors, data will be presented as odds ratios and their corresponding confidence intervals. Secondary analyses will be undertaken using the appropriate method for the outcomes, controlling where appropriate for intake values and other known prognostic variables using analysis of covariance. Simulations will be undertaken to encompass both screening approach groups and intention to treat analysis will be undertaken on both groups.

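### AED reattendance is given only a before-after comparison, with no randomised arm named and the 12-month window left open

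*Protocol*

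**What the plan says.** Under System measures the protocol states: "Reattendence to AEDs over the 6, and 12 month follow up period of patients participating in the study will be assessed using computerised admission records". The same sentence completes the plan for this measure: the result is to be "compared with admissions by the participating group of patients in the 6 month before entry into the study". No intervention arm or screening arm appears in it.

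The paragraph before it ends with a comparison between randomised departments: "We will also compare these measures between AEDs assigned to the SIPS-PAT versus the modified SASQ versus FAST screening methods". The measures meant there are those just listed, namely the screening rate, the proportion of screens that are positive, and the intervention rate. Reattendance is introduced only afterwards.

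Three other places bear on the point:

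- Design: "AEDs will be randomly allocated to one of three implementation conditions", with three AEDs in each.
- Economic evaluation: patient costs in the 6 months before screening and intervention are to be "compared to cost in the 6 month period after SBI to explore any changes in costs imposed by patients in each group".
- Planned analysis: secondary outcomes are to be analysed by a suitable method, "controlling where appropriate for intake values and other known prognostic variables using analysis of covariance". Reattendance is not named.

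**The concern.** The trial is randomised so that leaflet, brief advice and lifestyle counselling can be compared with one another. For reattendance, the one comparison written down sets the participants, described as a single group, against their own past.

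That contrast is weak here because of how patients enter. The inclusion criteria admit "Any AED patients scoring positive on the modified PAT, FAST or modified SASQ aged 18 or over", so every participant is caught at an attendance. People caught at an attendance tend to be in a period of higher than usual use, and their attendance can fall later with no help from the trial. A before-after difference mixes that fall with any intervention effect and cannot say which intervention, if any, did something.

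A second question arises at 12 months. The reference period is 6 months long, and the text does not say whether the later figure is a 12-month total, the second 6-month period, or a rate.

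Reattendance is taken from records and does not depend on a completed follow-up interview, whereas the sample size section allows for about 25% loss to follow-up. It could usefully support the randomised comparison, and the comparison as stated does not use it for that.

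**Working it through.** The protocol gives no attendance rate, effect size or power for reattendance, so there is no figure of its own to reproduce. The check has three parts.

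**1. Is an arm comparison stated anywhere for this measure?**

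| Place in protocol | Measure | Comparison stated | Arms named? | Windows |
|---|---|---|---|---|
| System measures, first paragraph | Screening, conversion and intervention rates | Between screening methods | Yes | Recruitment period |
| System measures, second paragraph | AED reattendance | After against before, in participants | No | 6 and 12 months against 6 months |
| Economic evaluation | Patient costs | After against before | By group | 6 months against 6 months |
| Planned analysis | Secondary outcomes in general | Suitable method, baseline adjusted | Not for reattendance | Not given |

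For costs, the protocol states both the grouping and equal windows. For reattendance it states neither.

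**2. What can the stated contrast identify?**

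Write the expected change in attendance in arm k as

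change(k) = d + e(k),

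where d is the change that would occur without any intervention effect (regression to the mean after selection at an attendance, plus time trend) and e(k) is the effect of arm k.

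- Pooled before-after: d + average of e(k). If every e(k) = 0, the result is d, which need not be zero.
- Between arms k and j: (d + e(k)) − (d + e(j)) = e(k) − e(j). The unknown d cancels if it is the same in both arms.

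The quantity d may differ by screening condition, because SIPS-PAT screening is targeted at presenting conditions linked to alcohol while FAST and the modified SASQ are universal. Table 1 of the protocol puts one AED in each of the nine cells, so each intervention arm contains one AED of each screening type. With screening condition in the model, such a difference is separated from the intervention contrast. The size of d cannot be computed from the protocol.

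**3. What do the windows alone do?**

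Assume a constant rate of r attendances per 6 months, no intervention effect and no regression to the mean.

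- 6 months after against 6 months before: r / r = 1.0.
- Cumulative 12 months after against 6 months before: 2r / r = 2.0, whatever r is.
- 12 months as a monthly rate: (2r/12) / (r/6) = 1.0.
- Months 6 to 12 alone against 6 months before: r / r = 1.0.

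So the mismatch exists only at 12 months, and only if the figure is an unscaled cumulative count.

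Parts 2 and 3 push in opposite directions: regression to the mean lowers the later count, and the longer window raises it. No net bias can be stated.

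**The case against.** The strongest reply is that the sentence sits under Measures, not under Planned analysis. It names a data source and a reference period and excludes nothing. The Planned analysis section sets intention to treat and baseline adjustment for secondary outcomes, and also provides for multi-level modelling. A pre-entry attendance count is a natural intake value for such a model. The choice of count model and similar detail commonly belong in a statistical analysis plan, which was not available.

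Much of this stands, and it limits the point in several ways.

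- A reader might infer that the protocol throws the randomisation away for this measure. It does not say so. It fails to state an arm comparison, and its general rule would permit one.
- A reader might infer unequal windows throughout. The 6-month comparison is matched, and the 12-month wording fits two successive 6-month periods or a rate as well as a cumulative count.
- A reader might suppose that the index visit is counted in the baseline. With assumed rates of 0.2 to 1.0 attendances per 6 months, that would give post/pre ratios from 0.2/1.2 = 0.17 to 1.0/2.0 = 0.50 with no effect. The rates are not in the protocol, and a window that ends before entry most naturally excludes the visit. These figures are not part of the finding.
- A reader might see two different events in reattendance and admissions. The Synopsis also speaks of admission rates of AEDs, so this is more likely loose wording for attendance.
- A reader might call this the only outcome free of self-report. The same section lists other recorded activity measures.

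What the reply does not remove is that the protocol is not silent. It states one specific comparison for reattendance, that comparison cannot address relative effectiveness, and a general rule that does not mention the measure does not clearly replace it.

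**Conclusion.** The point holds in a limited form. For AED reattendance the protocol states only a before-after comparison in the participating patients. Because they were selected at an attendance, a change from the pre-entry period can reflect regression to the mean and cannot be attributed to any of the three interventions.

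The size of that effect is unknown, since the protocol gives no attendance rates. At 12 months there is an additional factor of 2.0 if a cumulative count is set against the 6-month baseline, assuming a constant rate and no effect. There is none at 6 months, and none if rates or equal windows are used.

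Reattendance is secondary, is not named in the objectives or hypotheses, and plays no part in the sample size. The primary outcome is unaffected. The sentence should be amended, but it does not threaten the main result.

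**What to change.** Amend the reattendance sentence under System measures, or add a line under Planned analysis, to state that:

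- AED attendances after the index visit are compared between the randomised intervention arms at 6 and at 12 months, with screening condition as a factor and allowance for clustering by AED;
- the 6-month pre-entry count, index visit excluded, enters as baseline covariate;
- results use rates per unit of follow-up time, or equal 6-month windows;
- one term is used for the event, and it is defined as an AED attendance;
- before-after figures are shown by arm as description only.

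The cost is wording, because records for both periods are already to be used. The comparison will not be precise. With nine AEDs, fitting intervention and screening as main effects leaves 9 − 1 − 2 − 2 = 4 degrees of freedom at AED level, so the result should be reported with its confidence interval and read as supportive.
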